## 1.3 Summary

*Staphylococcus aureus* bacteremias (SAB) are major contributors to morbidity, mortality, and consequently healthcare costs (1,2). The SAB incidence in the Western world is approximately 26 per 100,000 population (3). About 2/3 of these infections are nosocomial-primarily catheter-associated-and about 1/3 are ambulatory-acquired (4-6). The 30-day mortality for nosocomial SAB was reported to be 22% in one study and 26% for ambulatory-acquired (4). Initial unpublished data from the AlertsNet project conducted at Jena University Hospital show a hospital mortality rate of 25%. Adequate treatment of SAB is nontrivial and includes proper choice and duration of antimicrobial therapy, infectious focus, and search for septic metastases and exclusion of infective endocarditis (1, 7). Data from nonrandomized and retrospective studies demonstrate that consultative co-management by clinical infectious disease specialists results in significantly improved survival, shorter hospital stays, and lower rates of complications, as well as reduced overall antibiotic use (8-17).

This is countered by the fact that a significant number of patients are treated in small and medium-sized hospitals. Due to the current shortage of clinical infectiologists, these cannot be cared for directly by one. In Thuringia, with more than 20,000 hospital beds, there are currently only 3 infectious disease specialist working in inpatient services. The requested cluster-randomized controlled cross-over SUPPORT study aims to test whether a telephone consultation by a clinical infectious disease specialist increases the survival of patients with SAB in Thuringia.

## 142 1.4 Synopsis

|                                              |                                                                                                                                                                                                                                                                                                                                                                                                                                                                                                                                                                                                                                                                                                       |
|----------------------------------------------|-------------------------------------------------------------------------------------------------------------------------------------------------------------------------------------------------------------------------------------------------------------------------------------------------------------------------------------------------------------------------------------------------------------------------------------------------------------------------------------------------------------------------------------------------------------------------------------------------------------------------------------------------------------------------------------------------------|
| Study title                           | Study of the Benefits of a Nationwide Outreach Program to Improve Outcomes in Patients with Staphylococcus aureus Bacteremia (SUPPORT Study) - a Single-Blind, Cluster-Randomized, Cross-Over Design Study.                                                                                                                                                                                                                                                                                                                                                                                                                                                                                    |

| Target population/disease             | Patients with Staphylococcus aureus bacteremia.                                                                                                                                                                                                                                                                                                                                                                                                                                                                                                                                                                                                                                                |
| Study design/methodology              | Prospective randomized, single-blind, controlled two-arm (intervention vs. control) multicenter trial with cross-over design. The intervention is the provision of a non-requested infectious disease telephone consult. The control group will not receive a telephone consult. The study duration in one group before cross-over is to be 12 months.
Randomization: 1:1 cross-over
Blinding: simple, i.e., patients are not told which group (intervention or control) they are in; blinding of treating physicians/study centers is not possible.
Intervention group: non-requested telephone consult.
Control group: no telephone consultation, follow-up only.
Follow-up: 90 days |
| Aims of the clinical trial/objectives | Primary Objective:
To demonstrate efficacy (30-day all-cause mortality) and safety of nonrequested infectious disease consults compared with standard care without telephone consults in patients with SAB.                                                                                                                                                                                                                                                                                                                                                                                                                                                                                 |

|                                                                 |                                                                                                                                                                                                                                                                                                                                                                                                                                                                                                                         |
|-----------------------------------------------------------------|-------------------------------------------------------------------------------------------------------------------------------------------------------------------------------------------------------------------------------------------------------------------------------------------------------------------------------------------------------------------------------------------------------------------------------------------------------------------------------------------------------------------------|
| Target variables/criteria/endpoints                      | 
Primary outcome measure: 30-day all-cause mortality (based on time of patient's SAB diagnosis).
 
Secondary targets:
 
 
– Fulfillment of the 6 defined quality indicators of SAB treatment until hospital discharge.
 
– 90-day all-cause mortality
 
– 90-day recurrence rate
 
– Progression of SAB to sepsis/septic shock over a 90-day period.
 
– Development of septic metastases over a period of 90 days
 
                 |
| Number of patients                                       | 
Evaluated for study inclusion: n=550
 
Patients included: n=500
 
Patients to be analyzed (minimum): n=450
 
(15 centers with an average of 2 (for the two study phases) x 15 patients).
                                                                                                                                                                                                                                                                                                          |
| Inclusion criteria                                       | 
All patients <math>\geq 18</math> years with 1st diagnosed SAB (positive blood culture). Re-inclusion if 2nd episode occurs > 90 days after 1st episode and there is no evidence of recurrence due to deep-seated infection.
                                                                                                                                                                                                                                                                           |
| Exclusion criteria                                       | 
 
– Positive blood cultures with only other pathogens in the blood culture
 
– Staphylococcus aureus infections without bacteremia
 
– Patients with therapy limitations or cessation, palliative care.
 
– Patients with a life expectancy < 90 days
 
                                                                                                                                                                                    |
| Treatments/procedures, treatment plan (incl. aftercare). | 
One-time performance of a non-requested case-based infectious disease consil.
                                                                                                                                                                                                                                                                                                                                                                                                                                    |
| Schedule                                                 | 
Patient-Related:
 
Duration of study-related measures: Follow-up duration: 90 days. Expected completion of last follow-up: April 30, 2018.
 
Study Related:
 
Start (date): August 1, 2015
 
Recruitment period: 24 months.
 
Inclusion 1st patient until end of follow-up last patient: 27 months
 
Total duration: 36 months.
 
Estimated completion date including evaluation: July 31, 2018.
                                                                |
| Study Centers                                            | 
Planned: n = 15 (participating hospitals of the AlertsNet project), listing in the appendix.
                                                                                                                                                                                                                                                                                                                                                                                                                     |
| Statistical methods                                      | 
Comparison of 30-day mortality between the intervention and control groups using a generalized mixed linear model (see the main body of the protocol for details). Null hypothesis testing was performed for the fixed effect group using the Wald test statistic with a two-sided significance level <math>\alpha=5\%</math>. Case number planning was done using simulations (see main body of the protocol for details) such that a power of 80% can be achieved to detect moderate to strong effects.
 |
| Funding                                                  | 
Federal Ministry of Education and Research (BMBF)
 
Funding code: FKZ 01EO1502
                                                                                                                                                                                                                                                                                                                                                                                                                              |

## 143 1.5 Schedule

144 In this regard, we refer to the schedule in **Chapter 4.6**.

## 1.6 Flowchart m

In this regard, we refer to the study schedule in **Chapter 7**.

## 1.7 List of abbreviations

|         |                                                            |
|---------|------------------------------------------------------------|
| CDDS    | Clinical Data Document System                              |
| EBCR    | Electronic Blood Culture Registry                          |
| CRF     | Case Report Form, Survey Form (paper-based or electronic). |
| FPI     | First Patient In                                           |
| GCP/GCP | Good Clinical Practice, Good Clinical Practice             |
| GLMM    | Generalized Linear Mixed Model                             |
| ITT     | Intention-to-Treat                                         |
| LPO     | Last Patient Out                                           |
| MDDS    | Medical Data Document System                               |
| MSSA    | Methicillin-sensitive Staphylococcus aureus         |
| MRSA    | Methicillin-resistant Staphylococcus aureus         |
| PPT     | Per Protocol Analysis                                      |
| SAB     | Staphylococcus aureus bacteremia                    |
| SIRS    | Systemic Inflammatory Response Syndrome                    |
| SOP     | Standard Operating Procedure                               |
| UKJ     | Jena University Hospital                                   |

## 2 Question or background

### 2.1 Initial situation

Bacteremias caused by methicillin-sensitive (MSSA) and methicillin-resistant (MRSA) *Staphylococcus aureus* strains are often complicated infectious diseases associated with high lethality and represent a separate entity due to the peculiarities in course, complications, and therapy (18). *Staphylococcus aureus* bacteremias (SAB) are relatively common, with an incidence of 22-32/100,000 (3) per year, and have a high lethality of up to 40% compared with other bacteremias (17, 19-21).

### 2.2 Question and justification of the project

The present study aims to answer the question to what extent non-requested telephone consultations by a clinical infectious disease specialist improve survival of patients with SAB in Thuringia.

### 2.3 Justification of the treatment and examination procedures

Data from nonrandomized and retrospective studies demonstrate that the inclusion of a clinical infectious disease specialist significantly improves the treatment and survival of SAB patients. Patients seen in consultation by an infectious disease specialist had higher rates of echocardiography, adequate duration of antibiotic therapy, and subsequently improved 30-day survival despite having more initial risk factors (8,9,17). A separate meta-analysis of 16 studies demonstrated that infectious disease consults can lead to a halving of SAB mortality (13% vs. 27%) (22). A recent study also demonstrated that adherence to an evidence-based bundle of measures improves the management of patients with SAB and reduces 14- and 30-day mortality (11). In contrast, a significant number of patients are treated in small and medium-sized hospitals and, because of the current shortage of clinical infectious disease specialists, cannot be directly managed by one. In Thuringia, with more than 20,000 hospital beds, there are currently only 3 clinical infectious disease specialist working in inpatient services.

The study aims to assess the extent to which non-requested telephone consultations in non-university hospitals in Thuringia significantly improve survival of patients with *Staphylococcus aureus* bacteremia. An overview of the procedure in the therapy arms is given in **section 7.1**. It is estimated that approximately 250 patients per year can be included in the study. If the study objectives can be confirmed by the results, it is conceivable that infectious disease telephone consults will be defined as the standard of care for all patients with SAB.

## 3 Study objectives

### 3.1 Primary study objective and primary endpoint

The primary study objective of the SUPPORT study is to determine whether 30-day all-cause mortality can be reduced in patients with SAB using telephone consults with a clinical infectious disease specialist in Thuringia (compared to no such telephone consults). This is a superiority study.

**Primary endpoint:** 30-day all-cause mortality

### 3.2 Secondary endpoints

The secondary endpoints of the SUPPORT study are:

- Fulfillment of the 6 defined quality indicators
- 90-day all-cause mortality
- 90-day recurrence rate
- Antibiotic therapy performed
- Progression of SAB to sepsis/septic shock over a 90-day period.
- Development of septic metastases over a period of 90 days

## 4 Study design and description

### 4.1 Type of study

SUPPORT is a controlled, cluster-randomized, single-blind, prospective cross-over study.

### 4.2 Type of therapy assignment

Participating hospitals will be randomized into two sequences before the start of the study. The randomization ratio for the two study arms is 1:1. It is intended to blind patients, i.e., no patient learns whether or not his or her treating physician receives a telephone consultation. Blinding of study physicians is not possible. The change from the intervention group to the control group or from the control group to the intervention group (cross-over) will take place for each hospital individually after inclusion of the 17th patient or after one year at the latest. The aim is to include a total of 30 patients per hospital.

### 4.3 Number and type of comparison groups

Two parallel groups will be formed. The first group represents the intervention group, in which randomized hospitals receive a non-requested telephone consult by a clinical infectious disease specialist when SAB is detected. The second group represents the control group, in which SAB is recorded and patients are followed up, but in which no nonrequested telephone consultation by a clinical infectious disease specialist occurs when SAB is detected. After inclusion of 250 patients, but no later than 12 months after initiation of inclusion, crossover of comparison groups occurs. That is, hospitals initially randomized to

the intervention group will now receive no unsolicited telephone consults when a patient with SAB is included. These patients will also be recorded and followed up. The hospitals that were initially randomized to the control group will then receive a non-solicited telephone consult when a patient with SAB is reported.

## 4.4 Scope of the study

The study will be conducted multicenter at at least 15 centers in Thuringia. A total of 500 patients will be included. The detailed case number calculation is presented in section 9.2.

## 4.5 Patient recruitment

As calculated in the "Case Number Planning" section, 550 patients with SAB will be screened and 500 patients will be enrolled in this study. The plan is to recruit this number of participants in at least 15 of the up to 39 centers participating in AlertsNet 2.0. The target number of participants per center is 17 per arm and phase, so that at least 15 patients per arm and phase will be available for evaluation.

With an estimated incidence rate between 22 and 32/100,000 person-years (3), between 500 and 700 SAB cases per year can be expected in Thuringia with a population of 2.2 million inhabitants. The case rate planning is presented in detail in **section 9.2**.

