## 5 Participating study centers

This study will include at least 15 of the up to 39 hospitals participating in AlertsNet 2.0 and a total number of 500 patients. Participating hospitals will be randomized into 2 groups with 2 sequences: A-B or B-A. Here, A represents the intervention and B the control group ("standard of care"). During the intervention, treating physicians at participating hospitals will receive unsolicited telephone consults recommending an evidence-based set of interventions to treat SAB (11).

The condition for participation here is that the laboratory to which a hospital sends its microbiological samples is connected to AlertsNet2.0. With regard to the IT concept, reference is made to the AlertsNet2.0 application.

Qualification of the participating centers or treating physicians beyond routine clinical work is not necessary. The telephone consultation is carried out by a clinical infectiologist or a physician with sufficient infectiological experience. There is no minimum number of patients to be included. The change of the groups takes place individually for each center after inclusion of the first 17 patients or after 12 months at the latest.

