### 9.3 Planning the scope of the study (case number planning)

Case number planning was performed for the primary end point, 30-day mortality, using the simulation software of Reich et al (25). A systematic review and meta-analysis were performed for case number planning (26). The meta-analysis, although not including any randomized trials, allowed estimation of the probability of patient death (within the 30 days starting from the time of SAB diagnosis) in the intervention vs. control group. This probability was estimated to be between 0.25 and 0.5 for the intervention group and between 0.5 and 0.7 for the control group. These probabilities translate into a relative risk of ~0.5. To detect such an effect with a power of >80% at a two-sided significance level of  $\alpha=5\%$  and low to moderate variation between study centers in the given design, at least 15 centers need to include an average of 2x15 patients (30 patients per cluster results in a total case number of 15x30=450 patients to be included). Since the follow-up visits consist only of telephone visits, which can also be answered by relatives of the patients, a low drop-out rate can be expected during the course. In order to be prepared for a possible drop-out, a total number of 500 patients is targeted.

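### The 17-patient switch rule makes 17 both target and ceiling of each hospital's first phase, so the stated minimum of 15 evaluable patients per arm and phase is not a property of the design

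*Protocol*

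**What the plan says.** - **Size.** The synopsis plans at least 450 patients for analysis, from "15 centers with an average of 2 (for the two study phases) x 15 patients". Section 9.3 asks for at least 15 centers with the same average and raises the total to 500 to cover drop-out.
- **Per-hospital target.** Section 4.5 turns this into "17 per arm and phase, so that at least 15 patients per arm and phase will be available for evaluation".
- **Switch rule.** Under 4.2 the arms change "for each hospital individually after inclusion of the 17th patient or after one year at the latest". Section 5 repeats this. Section 4.3 instead switches at 250 patients overall or 12 months, and the wash-out amendment speaks of 15 patients per institution.
- **Hospital volume.** Section 5 adds: "There is no minimum number of patients to be included". Section 5.2 does not restrict hospital size.
- **Accrual.** Section 2.3: "It is estimated that approximately 250 patients per year can be included in the study". Table 2 in 4.6 is faster, with the first patient at month 10 and the 250th at month 18.
- **End of enrolment.** Section 4.6 closes enrolment at the 500th patient.

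**The concern.** An average of 15 evaluable patients per phase lets busy hospitals make up for quiet ones. A ceiling removes that compensation. Under 4.2 and section 5 no hospital can put more than 17 patients into its first phase, yet the plan needs about 16.7 enrolled there on average (250/15). Quiet hospitals stop at 12 months with whatever they have. At stake are a per-phase figure that the design's own rule does not deliver, and the balanced 2 x 15 per hospital on which 9.3 is based.

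**Working it through.** **1. The plan's own figures reproduce.** 15 x 2 x 15 = 450, and 450/0.90 = 500, so a 10% loss is implied. Per phase this is 250 enrolled and 225 evaluable. The two-proportion normal approximation, ignoring clustering, is

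power = Φ{(|p1 − p2| − 1.96·√[2p̄(1−p̄)/n]) / √[(p1(1−p1) + p2(1−p2))/n]}.

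With n = 225 per arm it gives over 99.9% for 0.25 vs 0.50 and 99.2% for 0.50 vs 0.70. Both agree with the power above 80% claimed in 9.3. The simulation behind 9.3 cannot be repeated exactly, because the between-center variance is not given.

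**2. Margin under the ceiling.** 15 x 17 = 255 enrolled at most, against 250 needed. All 15 hospitals together may fall only 5 patients short of their ceilings.

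**3. Expected first phase.** Let X be a hospital's inclusions in 12 months. Its first phase holds min(X, 17), with mean E[min(X,17)] = Σ P(X > j) for j = 0 to 16. X is taken as Poisson for equal hospitals and gamma-Poisson for unequal ones. The CVs of hospital volume are assumptions, since the protocol gives none. Evaluable = 0.9 x enrolled.

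- Pace of 2.3: 250/15 = 16.7 per hospital-year.
- Pace of Table 2: 250 in 8 months is 375 a year, and 375/15 = 25 per hospital-year.

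| Pace per hospital-year | Volume CV | Mean per hospital | 15 hospitals, enrolled | Evaluable |
|---|---|---|---|---|
| 16.7 | 0 | 15.2 | 228 | 205 |
| 16.7 | 0.3 | 14.3 | 214 | 193 |
| 16.7 | 0.5 | 13.2 | 198 | 178 |
| 16.7 | 0.8 | 11.5 | 173 | 155 |
| 25 | 0 | 16.9 | 254 | 228 |
| 25 | 0.3 | 16.3 | 245 | 220 |
| 25 | 0.5 | 15.3 | 229 | 206 |
| 25 | 0.8 | 13.4 | 201 | 181 |

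At 16.7 without the ceiling, the first phase averages 250 enrolled and 225 evaluable, as planned.

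**4. The stated minimum of 15.** At 16.7 with equal hospitals, a hospital enrols at least 15 with probability 0.692. All 15 do so with probability 0.692^15 = 0.4%, even before any loss. The chance that the first phase reaches 250 enrolled is about 0.3%.

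**5. Hospitals needed.** 250/E[min(X,17)] at 16.7 per hospital-year is 250/15.2 = 16.4, so 17 hospitals if equal. It is 19 at CV 0.5 and 22 at CV 0.8. Keeping that rate in 17 to 22 hospitals implies 283 to 367 inclusions a year, not 250.

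**6. Effect on the contrast.** The second phase is not capped. If the total reaches 500, the phases split about 228/272 with equal hospitals and 198/302 at CV 0.5. The balanced-equivalent size, Σ 4·n1·n2/(n1+n2) over hospitals, was simulated at 16.7 per hospital-year. The window was 24 months, with a stop at 500 and a one-month wash-out after an intervention-first phase. Power is for 27% vs 13.5%, a halving of the 27% in 2.3, by the formula in step 1.

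| Volume CV | Size, 17-patient trigger | Size, fixed 12-month switch | Power |
|---|---|---|---|
| 0 | 473 | 469 | 95.7% vs 95.6% |
| 0.5 | 426 | 444 | 93.7% vs 94.5% |
| 0.8 | 383 | 425 | 91.1% vs 93.6% |

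After a further 10% loss, the gap is about 1 point at CV 0.5 and 3 points at CV 0.8.

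**The case against.** The other side has good arguments.

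- **The target is attainable.** 255 exceeds 250, and at the Table 2 pace equal hospitals deliver about 254. This stands, so one cannot say that the design is unable to reach its per-phase size. Whether it does depends on pace and on how alike the hospitals are.
- **Fifteen hospitals is a minimum in 4.4, 4.5, 5 and 9.3**, from up to 39. This stands too: more hospitals close the gap. But the protocol nowhere ties their number to the switch rule.
- **The primary analysis keeps every included patient and imputes missing endpoints.** On that reading 225 included per phase suffice. Equal hospitals then reach it with probability about 67%, but about 22% at CV 0.3 and 5% at CV 0.5.
- **The ceiling exists only under 4.2 and 5.** The rule in 4.3 has none, and under it the point disappears. The amendment's figure of 15, read as a trigger, would be tighter: at most 15 x 15 = 225 enrolled. The conflict has to be settled first.
- **The minimum of 15 may only explain the reserve of two patients.** That is a fair reading of intent, but the sentence is written as a result.

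A reader might also infer two stronger claims. One is that the total must fall well below 450. That would need a ceiling on the second phase, which no passage imposes. The other is that spreading the expected cases ("between 500 and 700 SAB cases per year can be expected in Thuringia with a population of 2.2 million inhabitants") over 39 hospitals shows each to be too small. That figure says nothing about the volume of the hospitals that join, and if all 39 took part the first phase would be far above 250.

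**Conclusion.** The point holds in limited form. Under 4.2 and section 5, 17 is both target and ceiling of the first phase, and nothing secures 15 evaluable patients per arm and phase. At 250 inclusions a year in 15 hospitals, the expected first phase is 228 enrolled / 205 evaluable with equal hospitals and 198 / 178 at CV 0.5, against 250 / 225. At the Table 2 pace it is met with equal hospitals and missed at CV 0.5 (229 / 206). The overall total can recover in the second phase, at the price of unequal phases within hospitals. The loss of power is about 1 point at CV 0.5 and 2 to 3 points at CV 0.8, so the trial's conclusion is not in danger. These sizes rest on Poisson accrual, assumed volume CVs, a 10% loss and power without clustering. The stated per-phase figure and the basis of 9.3 should still be corrected.

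**What to change.** 1. Reconcile the switch triggers: 17 per hospital in 4.2 and 5, 250 overall in 4.3, 15 per institution in the amendment.
2. In 4.5, replace the minimum of 15 per arm and phase with the expected yield per phase under the chosen rule.
3. Then choose one of two routes:
   - Keep the 17-patient trigger. Rerun the 9.3 simulation with capped, unequal phase sizes, and state the resulting power or the number of hospitals the rule needs (about 17 to 22 at 16.7 per hospital-year).
   - Make the 12-month date, already the phase length in the synopsis, the only trigger. Fifteen evaluable per phase is then a true average at the planned accrual.

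The cost is protocol wording and, on the first route, one simulation run; the stated power or number of hospitals may look slightly less favorable. On the second route, hospitals will differ more in size.
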